### Study blinding

The following people will be blinded as to which arm of the study the patient is allocated to:The patientThe functional assessor in the physiotherapy departmentThe University staff who assess the activity levels identified by the accelerometerThe physiotherapist providing post-operative physiotherapyThe radiologist reporting the CT scansThe 2 surgeons reporting the X-ray findings—no surgeon will report on his or her own patients

### Timescale

EKRU carry out 25 TKR procedures per month. We understand that studies have, on average, 54% of potential participants who choose not to be part of the research. Using this figure, we believe it is reasonable to recruit 11 cases per month. However, we will allow for 60 months to achieve our sample size of 126 bearing in mind the suspension of surgery that occurred between 2020 and 2022.

Each patient will remain part of the study for approximately 5 years.

Total duration of the study will be 11 years. This comprises 5 years to recruit participants, 5 years of follow up and data collection and one further year for data collation, cleansing and evaluation, statistical analysis and writing up of the study findings.

### Pre-operative radiological assessment

In addition to routine care, all study participants will undergo (1) a pre-operative CT scan of the affected leg which will be a spiral CT through the hip, knee and ankle, and (2) a whole leg antero-posterior radiograph standing on one leg (the leg about to have a TKR and involved in the study) and (3) a lateral “heel-hang” X-ray of the knee for surgery taken on a 17-inch X-ray plate.

### Pre-operative functional assessment

In addition to routine care, all study participants will attend the Functional Lab in the physiotherapy department at the RD + E Hospital for an assessment of their functional ability, using the Exeter Functional lab protocol and the InStride Accelerometer. The InStride accelerometer is a device used to measure speed of walking, stride length, equality of weight-bearing in walking. It is an app on a mobile phone. The patient clips the phone to their belt, walks 40 paces and the device measures the gait pattern and features. This is in addition to routine care.

In the subset of the first 40 participants selected to wear an activity monitor (accelerometer) physical activity will be assessed for 21 continuous days using a GENEActiv (ActivInsights Ltd, Kimbolton, UK) tri-axial accelerometer, measuring 43 mm × 40 mm × 13 mm. The GENEActiv will be attached to a polyurethane strap, and worn at the left wrist, like a watch. It can measure between ± 8 g at a rate of up to 100 Hz. During the proposed study, data will be collected at a rate of 20.0 Hz to permit 21 days of continuous monitoring.

Details of participants selected for physical activity monitoring will be sent to the research team in the Department of Sport and Health Sciences at the University of Exeter, St Luke’s campus. They will send out accelerometers at each time point with prepaid return envelopes along with a participant guide for wearing the accelerometer and a short log for recording when the device was fitted and removed. Participants will also be asked to record the time they go to bed and get up each day to assist with data analysis.

### Intra-operative assessment

Based on pre-operative CT scans, the MAKO system generates a 3D computer image of a patient’s knee joint.

This unique 3D computer image is used by the surgeons to determine how much bone to remove and where to place the knee replacement implants.

### Post-operative follow up

Participants will be reviewed at 6 weeks, 3 and 6 months, 1, 2 and 5 years post-operatively. The 3 and 6 month appointments are in addition to routine care. The 1, 2 and 5 year follow ups are usually done by postal questionnaire but will require hospital attendance in Exeter for the purpose of the study as they will undergo a repeat of the functional testing at each time interval. The 6 post-operative visits for functional testing are in addition to routine care.

The cohort of 40 patients who used the activity monitoring accelerometer provided by the Department of Sports Science at Exeter University pre-operatively will be given another device whilst an in-patient in hospital. This will be worn continuously for a further 21 days before being returned to the University in a stamped addressed envelope that has been provided for that purpose. This will accurately log their post-operative activity levels. The cohort of 40 patients who used the activity monitoring accelerometer provided by the Department of Sports Science at Exeter University pre-operatively will be posted another device 3 months after surgery. This will be worn continuously for a further 21 days before being returned to the University in a stamped addressed envelope that has been provided for that purpose. This will accurately log their 3-month post-surgery activity levels.

### Post-operative radiological assessment

Participants will undergo X-ray examination of the knee post-operatively whilst in hospital and then at 6 weeks, 2 and 5 years.

Participants will undergo one post-op CT scan examination of the affected leg at approximately 6 weeks after surgery which will be a spiral CT through the hip, knee and ankle and a repeat of the whole leg antero-posterior radiograph standing on one leg (the leg that has just had a TKR and is involved in the study) at 6 weeks post-operatively. This is in addition to routine care.

### Assessment of outcome

We will assess the results in a number of different ways including validated patient generated outcome questionnaires, functional assessment (strength, flexibility and the ability to carry out everyday tasks such as rising from a chair, climbing stairs, walking on rough ground), measurement of activity levels and radiological assessment of alignment.

### Primary outcome measure

The assessment of difference in function between the 2 study groups as measured by the OKS. The MCID for this outcome measure is 5 points. We will assess this at 1 year post surgery.

### Secondary outcome measures

Assessment of peak quadriceps muscle torque measured by myometer at 6 weeks, 3 and 6 months and 1, 2 and 5 years post op.Measurement of length of stay (LOS) in hospitalMeasurement of lower hospital costs as a result of reduced LOS assessed between the arms of the studyAssessment of hamstrings muscle mass/torque measured by myometer at 6 weeks, 3 and 6 months and 1, 2 and 5 years post-op.Patient generated outcome scores (KOOS, EQ5D, the Forgotten Knee Score (FKS), UCLA activity score, SF36 at 6 weeks, 6 months and 1, 2 and 5 years post-op.Assessment of function using the Exeter Functional lab protocol at 6 weeks, 3 months, 6 months, 1, 2 and 5 years post-op.Assessment of function using the Instride AccelerometerAssessment of activity levels as measured by an accelerometer used for 21 days at the pre-surgery, post-surgery and 3 months after surgery time frames.Self-Assessment of Patient Satisfaction via SAPS questionnaire at 6 weeks, 6 months, 1, 2 and 5 years post op.Assessment of positioning of the implants and of joint line position by a comparison of pre-op and 6 weeks post op CT scans. Measurement of range of movement of the knee at 6 weeks, 3 months, 1, 2 and 5 years post-op.Assessment of wear of the prosthesis on X-ray at 6 weeks, 2 and 5 years.Any significant differences in component positioning measured on the full leg alignment X-ray at 6 weeks.Any significant differences in limb alignment measured on the full leg alignment X-rays at 6 weeks

### Surgery

The standard MAKO TKR protocol will be followed with separate algorithms for the 2 alignment philosophies. A template operation note has been included as Appendix 1. Alignment of the components which will be decided upon in the randomisation schedule for use of the traditional mechanical alignment or the alternative alignment technique. The 4 surgeons involved in this study are all experienced TKR surgeons.

All components will be cemented in situ. All patients receive the Triathlon CR Implant with an X3 polyethylene insert. All patellae will be resurfaced.

After surgery, patients will be discharged home allowed to fully weight-bear as comfort allows and with walking aids for use for a 6-week period if required. All patients will have been instructed in an exercise regime whilst in hospital which they will continue after discharge and post-operative out-patient physiotherapy will be provided on an as needed basis. The physiotherapy treatment (type and frequency) will be decided upon by the individual physiotherapist seeing each patient. This reflects the care given to TKR patients in a part rural region and mirrors the care available which is given on an as needed basis.

### Data collation

To be undertaken by the clinician undertaking the specific procedure concerned.

[name] or the research nurses attached to the RD + E Hospital R + D department will collect the pre-op consent, the pre- and post-op PROMs. Data will be entered on to the study database by them the accuracy of entry double checked by them i.e. one person enters the data and a second checks its accuracy.

RD + E Hospital physiotherapists will be responsible for collection of the Functional Assessment data.

Colleagues at the University of Exeter will be responsible for collating the accelerometer data on the participants who use the 21-day device. Data returned via the post will be downloaded using GENEActiv PC software version 1.4 and analysed using the GGIR software package for R (cran.r-project.org). Data Time spent in different physical activity intensities will be estimated using published accelerometer cut-points.

The 4 surgeons will be responsible for clinic data and communications, operation note details, reporting on X-ray findings- all of these to be on the hospital Clinical Documentation Management system.

CT scan findings will be reported as with any CT scan undertaken within our hospital. The data from the CT scan and X-ray images will be used by Stryker US client application to direct the surgeon via the MAKO system in how to perform the bony cuts on each participant.

Data from the InStride accelerometer will be collected separately and using only the patient’s unique study number for identification. The data is captured on an I-phone specifically purchased for this purpose by our Unit. The accelerometer includes a Clinician Mode accessed through a secure authorization code that allows the capture of walk patterns in a clinical setting with the walk data stored only on the app portal. In this mode no data is stored on the Smartphone used to capture the walk.

Similarly, secure clinician access to the InStride Web portal allows download of the unprocessed triaxial accelerometer data in addition to viewing the users five walk parameters.

All other data will be stored on RD + E NHSFT secure computers. Data will be entered into an Excel spreadsheet for later transfer into a statistical package such as SPSS v24, for analysis. All patient identifiers will be removed. The study data will be entered by a data clerk and double checked by either the study-co-ordinator or one of the research nurses. At the end of the study, when all analysis of the data has been completed, the study data will be archived as per our sponsor’s archiving SOP.

## Statistical analysis

Independent statistical analysis of the results will be undertaken by an experienced statistician from the R + D department within our hospital.

All outcomes will be reported descriptively by group, with continuous outcomes reported as mean (standard deviation) or median (interquartile range).

All continuous outcome measures, including the primary outcome (OKS) will be analysed using linear regression modelling with adjustment for randomisation variables (surgeon, severity based on baseline OKS, and age (below 70, 70 and above), and baseline measurement). EQ5D will be analysed using the equivalent analyses with Tobit regression. Between group comparisons will be reported using confidence intervals and p-values.

For continuous measures recorded at multiple time points, hierarchical regression models will be used to assess the interaction between intervention and timepoint, with the interaction effect reported as a global p-value.

All analyses will be reported using the intention to treat principle. The primary analyses will include complete case data only. The amount of missing data will be reported for all outcome variables. In the event of substantive missing data (more than 5%), a secondary analysis will be performed including observed data and missing data imputed using multiple chained equations.

## Dissemination of results

The participants will be informed in writing of the results if they so desire. The Research and Development Office at the RD + E will be informed of the results.

We plan to present the results both nationally and internationally at knee surgery conferences and to publish the results in a peer reviewed journal.

### Impact of research

The impact of this study as yet is unknown. If we identify a clear advantage of one study arm over the others, then it is likely that this technique will become our standard TKR procedure- with the aim of providing patients with the best clinical and functional results after their TKR surgery. Similarly, if a clear difference is found in one study arm, one would hope that presentation of the results to colleagues at other institutions will result in better long-term results for their patients.

In the event that no technique proves superior to the others, then this will provide surgeons with the reassurance that no matter what their preferred technique, their patient is not being disadvantaged.

If one arm of the study out performs the other in clinical and functional results, there may also be cost differences between the arms of the study which could result in cost savings for the NHS.

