### Sample size

126 patients (63 per arm). The sample size was determined using the primary outcome measure, OKS measured at 12-month follow-up, which has an MCID of 5 units [14]. To detect a between group mean difference of 5 units, with 90% power and significance threshold of 0.05, using a standard deviation in both groups of 7.6, requires 50 participants per group. Thus, accounting for drop-outs, we aimed to recruit an additional 13 patients to each arm, bringing the total to 126 patients. For a completed SPIRIT checklist, see the additional file. [13]

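### The impact section takes a failure to show superiority as reassurance of no disadvantage, although a non-significant result here can still be compatible with the 5-point MCID

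*Protocol article*

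**What the plan says.** The primary aim (Study aims and objectives) is to show that alternative alignment gives a better 1-year OKS than traditional alignment, judged against an MCID of 5 points. The Sample size section matches that aim: "To detect a between group mean difference of 5 units, with 90% power and significance threshold of 0.05". Taking an SD of 7.6 in each arm, it arrives at 50 evaluable patients per arm. It then adds a dropout allowance: "we aimed to recruit an additional 13 patients to each arm, bringing the total to 126 patients".

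Statistical analysis plans an adjusted linear regression on complete cases, with group comparisons given as confidence intervals and p-values. The document states no equivalence or non-inferiority hypothesis or margin.

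Impact of research then says what a null result would mean. The condition is "In the event that no technique proves superior to the others", and the consequence is that "this will provide surgeons with the reassurance that no matter what their preferred technique, their patient is not being disadvantaged". Nothing else is required: the sentence mentions no interval, no margin and no particular outcome.

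**The concern.** Failing to show that one technique is better does not show that neither is worse. Whether a null result is reassuring depends on which differences the confidence interval rules out, and the sentence does not ask. It is also unlimited in scope. The sample size rests on 1-year OKS alone, while the secondary outcomes include strength, satisfaction and prosthesis wear, some of them followed to 5 years.

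The article plans conference presentations and journal publication, and the sentence is addressed to surgeons choosing a technique. If it were carried into the trial report, surgeons could be told that the choice does not matter on data that leave a difference of the full MCID open.

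**Working it through.** **Inputs, all from Sample size unless noted.** Difference 5; SD 7.6 in each group; power 90%; threshold 0.05; 50 evaluable per arm; 63 per arm recruited. Three assumptions are mine:
- The test is two-sided. Sidedness is not stated, but a one-sided test would need only 40 per arm.
- The intervals are 95%, to match the threshold.
- 7.6 is the SD that remains after covariate adjustment.

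**Step 1: reproduce the plan's figure.** n = 2 × (1.960 + 1.282)² × 7.6² / 5² = 48.6, so 49 per arm by the normal approximation. The t-test gives 49.5, so 50, as stated. With 20% loss, 50 / 0.80 = 62.5, so 63, also as stated (13/63 = 20.6%). The superiority calculation is sound.

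**Step 2: width of the interval.** SE = 7.6 × √(2/n); half-width h = t × SE. An estimate is non-significant if its size is below h. Its interval reaches 5 if its size is at least 5 − h. The far limit of a non-significant result can approach 2h.

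| Evaluable per arm | SE | h | Non-significant, yet interval includes 5 | Far limit up to |
|---|---|---|---|---|
| 50 | 1.52 | 1.984 × 1.52 = 3.02 | about 2.0 to 3.0 | about 6.0 |
| 63 | 1.35 | 2.68 | about 2.3 to 2.7 | about 5.4 |

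**Step 3: how often this happens.** For a true difference d, using the normal distribution around the t-based h:

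P(non-significant) = Φ((h − d)/SE) − Φ((−h − d)/SE).

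The share whose interval includes +5 or −5 follows by counting only estimates with size between 5 − h and h.

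| True d | Non-significant, 50 per arm | Of these, interval includes ±5 | Non-significant, 63 per arm | Of these, interval includes ±5 |
|---|---|---|---|---|
| 0 | 95% | 15% | 95% | 4% |
| 3 | 50% | 50% | 41% | 24% |
| 5 | about 10% | 75% | about 4% | 45% |

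For example, at 50 per arm and d = 5: Φ((3.02 − 5)/1.52) = Φ(−1.30), about 0.10.

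**Step 4: would a rule based on the interval be usable?** With no true difference, the chance that the whole 95% interval lies within ±5 is 0.953 − 0.145 = 0.81 at 50 per arm and 0.952 − 0.039 = 0.91 at 63.

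**Step 5: sensitivity to the SD.** The document gives no correlation between baseline and 1-year OKS. If 7.6 is the unadjusted SD and the correlation is r, the half-width shrinks by √(1 − r²). Using 1.96, the largest far limit at 50 per arm is 5.96 × √(1 − r²): 5.7 at r = 0.3, 5.2 at r = 0.5 and 4.8 at r = 0.6. It falls below 5 once r exceeds about 0.54. At 63 per arm (5.31 × √(1 − r²)) it does so once r exceeds about 0.34. In the other direction, an assumed SD of 9 to 10 gives half-widths of 3.5 to 3.9 at 50 per arm, and the problem grows.

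**The case against.** The sentence is in a section on impact, which opens by admitting that the impact is not yet known. A reader might infer that the plan has adopted a rule treating a p-value above 0.05 as proof of equivalence. The documents do not support that: the text speaks of reassurance, and Statistical analysis contains no such rule. That section also commits to reporting confidence intervals, and the MCID is fixed elsewhere, so readers of the results would have the means to judge for themselves.

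A reader might also infer that a null result is the expected outcome, because the Introduction cites a meta-analysis of 30 studies that found no significant difference in patient-reported outcomes. But the Introduction also cites a comparative study with a 7-point OKS difference in favour of kinematic alignment. A null result is plausible; the article does not make it the likely one.

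On size, the 10% miss rate at a true difference of 5 is simply the type II error that a 90% power design accepts. A true difference of 3 lies below the MCID, so calling it unimportant would not be false by that benchmark. With no true difference, about 85% of non-significant results at 50 per arm would exclude ±5. The figures at 50 also assume that the whole dropout allowance is used and that adjustment gains nothing.

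All of this stands, and it limits the severity. It does not rescue the sentence, which grants reassurance whatever the interval shows and for every outcome.

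**Conclusion.** The concern holds at moderate severity. Impact of research draws an unconditional no-disadvantage conclusion that a superiority design without an equivalence margin cannot support. With 50 evaluable per arm, SD 7.6 and no gain from adjustment, non-significant estimates of about 2.0 to 3.0 points leave the 5-point MCID inside the 95% interval, and a true 5-point difference is missed about 10% of the time. With 63 evaluable per arm the band narrows to about 2.3 to 2.7 points and the miss rate falls to about 4%. With a strong baseline correlation a non-significant interval may be unable to reach 5 at all.

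Even then the sentence is too broad, because it does not check the interval and covers outcomes for which no sample-size basis is given. The sample size calculation and the primary test are not in question.

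**What to change.** Replace the sentence in Impact of research with wording such as:

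> If superiority is not shown, we will report that no difference was shown and will interpret the 95% confidence interval for the adjusted 1-year OKS difference against the 5-point MCID. We will state that a clinically important difference in 1-year OKS has been excluded only if the whole interval lies between -5 and +5; otherwise the result is inconclusive. This conclusion does not extend to secondary or longer-term outcomes such as wear.

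The 5-point bound is proposed because it is the only benchmark that the document gives. If the investigators consider a smaller difference important, they should name it before results are known, and should expect the trial to exclude it less often.

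The cost is wording only: no extra patients and no new analysis, since confidence intervals are already planned. The drawback is that some null results must be reported as inconclusive. If there is truly no difference, about 19% of all results at 50 per arm (100% − 81%) and 9% at 63 (100% − 91%) would not meet the ±5 condition. These figures include the 5% or so that are significant by chance.

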## Patient involvement

We have consulted with patients on the feasibility of participating in the study at all and in particular about the demands of attending the appointments for functional assessment and CT scans. The study was discussed at our patient research panel. This panel is a group of patients who have undergone knee replacement surgery in our Unit and who are therefore, well placed to comment on the practicalities of study involvement, as well as on the appropriateness and clarity of the patient information leaflet. Attendance at all time frames is critical for completion of the secondary measure functional outcome and it was stressed by our patient representatives that the patients need to be fully informed of the commitment required should they agree to take part. Similarly, it was recommended that the extra commitment for CT scan appointments be highlighted.

We hold bi-annual meetings of the patient research panel and if issues arise when running the study that require further patient involvement, we will take them to the panel for consultation. If a meeting is not due for some time, we will contact a panel member personally for their advice.

When we consulted on the design and wording of the patient information leaflet and the consent form, various changes were recommended and implemented.

